## Abstract

Anticholinergics have been shown to enhance quality of life and reduce sweat in patients with hyperhidrosis. However, it remains unclear whether topical application specifically exerts local or systemic effects. This study’s primary aim is to assess topical oxybutynin’s impact on axillary hyperhidrosis. Twenty patients will be randomized into three groups. Group A will receive 2.5 mg of oral oxybutynin from day 1 to day 35 (on a variable frequency regimen). Group B will be administered a topical placebo for 35 days and Group C will receive a 10% oxybutynin topical spray, to be used twice daily for 35 days. The primary efficacy outcome will be the evaluation of the effectiveness of topical oxybutynin spray in treating hyperhidrosis. The TODAY trial will generate high-quality evidence on the effects of topical oxybutynin, assessing whether its impact is local or systemic in patients with axillary hyperhidrosis.

## INTRODUCTION

Hyperhidrosis (HH) is a condition characterized by excessive sweating, exceeding the level necessary for regulation of body temperature.^1^ It affects approximately 15.3 million individuals in North America.^2^ The etiology of primary HH remains poorly defined, but it is believed that it involves hyperactivity of the sympathetic nervous system caused by genetic predispositions.^3^ Hyperhidrosis has a significant impact on quality of life (QoL) and is associated with similar social and professional stigma to chronic conditions such as severe psoriasis. Individuals with HH also have higher rates of depression and anxiety.^4^ Primary HH, also known as idiopathic HH, accounts for around 90% of HH cases and the armpits are the most affected area.^3^ This form of HH generally starts in adolescence and tends to worsen over the years.^5-7^

Current treatment options for HH include video-assisted thoracoscopic sympathectomy (VATS), botulinum toxin injections, a range of topical treatments, and oral anticholinergics, but efficacy is variable and they can cause significant side effects.^8,9^ A long-term study involving 1,685 cases of primary HH treated with oral oxybutynin demonstrated improved quality of life and reduced HH severity, as measured by the hyperhidrosis disease severity scale (HDSS), although 24.9% of the patients experienced intense dry mouth.^10^ There are a limited number of reports of use of topical anticholinergics and of topical glycopyrrolate in the form of pads and creams, and of oxybutynin in gel form, which demonstrated efficacy.^11-14^

## BACKGROUND AND STUDY OBJECTIVES

Topical oxybutynin spray is easier to use, but has not previously been tested. The benefit of using an oxybutynin 10% spray for axillary HH would be expected to accrue from its limited systemic effects, which could reduce the sympathomimetic side effects observed with oral anticholinergic and so potentially improve adherence to treatment, improving both QoL questionnaire scores^15^ and HDSS scores.^16^

This phase II trial will assess the efficacy of a topical oxybutynin 10% spray applied twice a day, in comparison to a placebo and to oral oxybutynin in patients with axillary HH.

## METHODS

### Study design

TODAY (ClinicalTrials.gov: NCT05102396) is a pragmatic, randomized trial, conducted by academic investigators from multiple centers. The name is an acronym derived from the title “***TO***
*pical oxybutynin for hyperhi*
***D***
*rosis:*
***A***
*topic or s*
***Y***
*stemic effect*”.

The study design is Prospective Randomized Open Blinded Endpoint (PROBE) and approximately 21 patients on anticholinergic treatment with a confirmed diagnosis of HH will be recruited, as illustrated in Figure 1.

**Figure 1 gf0100:**
[figure not shown]
Study design of the TODAY clinical trial (topical oxybutynin for axillary hyperhidrosis).

The TODAY trial is part of a register of all patients with HH admitted at two centers in Brazil. The first 20 eligible individuals among these patients diagnosed with axillary HH will be invited to take part in the trial, which will involve randomization to withdraw other HH treatments for 30 days. The baseline characteristics and the outcomes will be recorded using a Case Report Form (CRF).

The Brazilian Ministry of Health’s National Research Ethics Commission (CONEP - Comissão Nacional de Ética em Pesquisa) approved the study protocol (CAAE 30283520.0.0000.5479; decision 3.978.439). The study will follow the protocol and will be entirely compliant with Helsinki Declaration ethical principles and the International Council for Harmonisation Guideline for Good Clinical Practice. The study protocol requires informed consent from each patient before any study procedures are initiated.

Clinical diagnoses will be made by a trained team member using standard clinical assessments; imaging is unnecessary. Patients will be considered eligible if they have a symptomatic HH score ≥ 52 on the QoL scale, have signed the informed consent form (ICF), responded to the HDSS, are aged from 18 to 45 years, and have no history of sympathectomy. The authors have listed detailed inclusion and exclusion criteria in Table 1.

**Table 1 t0100:** Inclusion and exclusion criteria for the TODAY clinical trial (topical oxybutynin for axillary hyperhidrosis).

Inclusion criteria
1. Patients aged ≥ 18 years and ≤ 45 years
2. Patients who have not been treated with other medication or other treatment method therapeutic for the disease in the previous 30 days
3. Quality of life (QOL) ≥ 52
Exclusion criteria
1. Patients with hypersensitivity to oxybutynin hydrochloride
2. Patients who have been treated with other medication or other treatment method therapeutic for the disease in the previous 30 days
3. Patients with symptoms related to menopause
4. Patients with signs of skin changes in the axillary area
5. Pregnancy. Women with the potential to conceive and gestate who are not using contraceptive strategies and have not had a negative pregnancy test
6. Patients with Covid in the contagious phase (PCR+)

### Randomization and intervention

#### Randomization

Participants will be randomized into three treatment groups using a computer-generated randomization schedule prepared in advance of the study. In Group A, patients will be given oxybutynin at a dosage of 2.5 mg once a day, at night, for the first 7 days, followed by 2.5 mg twice a day from day 8 to day 21 and then 5 mg twice a day from day 22 to day 35. Group B will be given a topical placebo similar to the oxybutynin spray administered in two sprays into each armpit twice a day for 35 days. Group C will be given a topical oxybutynin 10% spray, also administered in two sprays into each armpit twice a day for 35 days.

Baseline characteristics will be recorded, and will be randomized electronically at a proportion of 1:1:1, balance with random sized blocks. This study will employ an open blinded endpoint design (Figure 2).

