### Assessment of sweating

Devices that measure evaporation of sweat from the skin or the sweat can quantitatively assess diaphoresis. However, such instruments may not accurately reflect the daily discomfort undergone by individuals with HH. Therefore, patient-reported results are crucial to assess the impact of HH.^17^ The HDSS and the QoL questionnaire objectively assess the progression of HH. QoL assessments are essential tools in medical research, because they enable collection of high-quality data for diagnosis and monitoring of patients’ results. The impact of HH on QoL is well-documented, with easy-to-use questionnaires that are essential for clinical assessments.

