## CONCLUSIONS

The TODAY study is a phase II trial with a Prospective Randomized Open Blinded Endpoint (PROBE) design that will recruit patients diagnosed with axillary HH. The objective is to determine and assess the impact of topical oxybutynin on axillary HH. The study results will help guide medical decision-making with respect to the best way to manage axillary hyperhidrosis.

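### The blinded-endpoint label does not protect the efficacy endpoints, because the patient scores both of them in a trial declared open, including for spray versus placebo

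*Protocol article*

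**What the plan says.** The design is named three times in the protocol article, each time for the trial as a whole:

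- Study design: "The study design is Prospective Randomized Open Blinded Endpoint (PROBE) and approximately 21 patients on anticholinergic treatment".
- Randomization: "This study will employ an open blinded endpoint design (Figure 2").
- Conclusions: "phase II trial with a Prospective Randomized Open Blinded Endpoint (PROBE) design".

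None of these places excepts the two spray arms, and no section states that patients are masked.

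On the two sprays, the Randomization section says "Group B will be given a topical placebo similar to the oxybutynin spray", and describes the active spray as "also administered in two sprays into each armpit twice a day for 35 days". Sites, number of sprays, frequency and duration are therefore the same in Groups B and C.

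The section on primary efficacy endpoints names HDSS improvement and response at day 35, together with the quality-of-life questionnaire. The sections on the two instruments say that the patient answers each of them. The Discussion (Assessment of sweating) sets instrument measurement of sweat aside in favour of patient-reported results, yet also says: "The HDSS and the QoL questionnaire objectively assess the progression of HH".

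**The concern.** An open trial with blinded endpoint assessment accepts that patient and clinician know the treatment. It relies on an assessor who does not know it to keep the outcome unbiased. That works when the outcome is scored by someone other than the patient. Here the patient is that assessor, and masking whoever hands out or enters the questionnaire does not mask the answer.

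Expectation can act directly on the primary endpoint. A responder needs a one-point change on a four-level self-rating, a threshold that belief about treatment could move. The oral arm is distinguishable from a spray unless a double dummy is used, so some openness there is hard to avoid. Between the two sprays it looks avoidable, and that comparison carries the stated expectation that the spray is superior to placebo. If it is run open, a difference between C and B cannot be separated from patients' knowledge of what they received.

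**Working it through.** **Who knows, and who scores**

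| Item | What the protocol article states | Section |
|---|---|---|
| Treatment assignment | Open, for the whole study | Study design; Randomization; Conclusions |
| HDSS scored by | Patient | Hyperhidrosis disease severity scale |
| QoL scored by | Patient | Quality of life questionnaire |
| Efficacy measure scored by an independent masked assessor | None named | Primary efficacy endpoints |
| Placebo spray | Similar to the active spray, same regimen | Randomization |

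The first three rows together mean that the assessor of each efficacy endpoint knows the allocation.

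**Size (illustration only)**

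The article gives no test, significance level, responder rate or estimate of reporting bias, so there is no stated figure to reproduce.

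Inputs:
- From the document: 1:1:1 allocation of about 21 patients (21/3 = 7 per arm) or 20 (20/3 = 6.67).
- Assumed: no true drug effect; a response rate p of 30% to 70% if masked; knowledge of allocation moves the reported rate to p + s in C and p − s in B; a two-sided 5% Fisher test; equal arms of 6 or 7.

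Bias in the estimate: (p + s) − (p − s) = 2s. A shift of 10 points each way creates a 20-point apparent effect; 20 points each way creates 40.

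Chance of significance favouring the spray: the sum of P(C = c) × P(B = b), both binomial, over the tables that reach p ≤ 0.05. With 7 per arm these tables are (c, b) = (5,0), (6,0), (7,0), (6,1), (7,1), (7,2).

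- 50% vs 50%: (21 + 7 + 1 + 49 + 7 + 21)/2^14 = 106/16384 = 0.6%.
- 60% vs 40%: P(C = 5, 6, 7) = 0.2613, 0.1306, 0.0280, and by symmetry P(B = 2, 1, 0) takes the same values. Sum: 0.0073 + 0.0037 + 0.0008 + 0.0171 + 0.0037 + 0.0073 = 4.0%.
- 70% vs 30%: the values are 0.3177, 0.2471, 0.0824. Sum: 0.0262 + 0.0203 + 0.0068 + 0.0610 + 0.0203 + 0.0262 = 16.1%.

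Chance that the spray merely looks better (C > B): at 50% vs 50% with 7 per arm, ties have probability 3432/16384 = 0.2095, so it is (1 − 0.2095)/2 = 39.5%. The other cases are summed in the same way.

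Over base rates of 30% to 70%:

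| Shift each way | Significant, 7 vs 7 | Significant, 6 vs 6 | Looks better, both sizes |
|---|---|---|---|
| 0 | 0.3-0.6% | 0.2-0.3% | 38-40% |
| 10 points | 2.8-4.0% | 1.2-2.0% | 67-71% |
| 20 points | 13.3-16.1% | 6.4-8.5% | 88-93% |

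These ranges are for equal arms. Twenty patients split as evenly as possible are 7, 7 and 6, so B versus C could be 7 vs 6. Fisher's test is less conservative there, and the same sum gives about 0.5-1.1%, 3-6% and 14-21% for significance. The pattern is the same.

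**The case against.** The strongest reply is that the article never says patients in B and C are told which spray they have. A reader might infer from the design label that they are. A similar placebo on an identical regimen fits just as well with an unstated mask between the sprays, with openness meant only for oral versus spray. The article condenses a fuller protocol, and the figures it cites are not shown. This stands as a limit: the text does not establish that B and C patients will know their spray. It does not rescue the label, which is applied to the whole study, and Figure 2 is cited for that same open design. If a mask was intended, the label is wrong for B versus C. If not, the comparison is open.

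Other tempting readings also go too far:

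- **The placebo is already matching.** The article says similar. Appearance, smell and packaging are not described, so it is not shown that coding needs labels alone.
- **The label is wholly empty.** Handling of the questionnaires, or the proportional adjustment of QoL scores, could be masked. That would leave the patient's own expectation untouched.
- **Spray versus placebo is the only efficacy comparison.** Oral oxybutynin is also an efficacy comparator.
- **A 16% false-positive rate is the expected harm.** The test, base rate and shifts are assumptions. In the smaller equal-arm case a 20-point shift each way gives 6-9%, and every 10-point result with equal arms stays below 5%.

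The Discussion's claim of objectivity sits beside its own description of the outcomes as patient-reported, so it does not hide who scores. It is still the wrong word.

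**Conclusion.** The point holds. The protocol declares the whole trial open with a blinded endpoint, and the patient scores both efficacy endpoints, so the label does not guard either against expectation bias. As written, the spray-versus-placebo comparison is open as well. The documents do not support the stronger claim that patients will in fact be told which spray they have; they support a conflict between the design label and the presence of a similar placebo.

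The size cannot be taken from the documents. Under the assumptions above, the main harm is to the estimate and its apparent direction: a reporting shift of 10 points each way takes the chance that an ineffective spray looks better from about 38-40% to 67-71%. This matters for a small phase II trial that hopes to show a trend and lead to larger studies. Inflation of significance is secondary and depends more on the assumptions. The point concerns efficacy endpoints only. No later analysis can remove the bias from data collected open, so it needs settling before the data are collected.

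**What to change.** 1. Confirm that the two sprays are indistinguishable in appearance, smell and packaging. Then supply them in coded bottles, with the code held away from patients and site staff until database lock.
2. State that B versus C is double-blind.
3. Describe Group A, and the C-versus-A comparison, as open-label with self-reported outcomes, and interpret it that way.
4. Replace the PROBE label in the Study design, Randomization and Conclusions sections, and drop the word objectively for the two self-report scales.

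If a mask between the sprays is already in place, only the wording in steps 2 to 4 needs to change.

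Cost: a short amendment, coded labelling and someone to hold the code, and possibly some formulation or packaging work if the sprays are not yet identical. Sample size, visits and regimens do not change.

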**Figure 2 gf0200:**
[figure not shown]
Flow diagram for the TODAY clinical trial (topical oxybutynin for axillary hyperhidrosis). QoL = quality of life; HH = hyperhidrosis; HDSS = Hyperhidrosis Disease Severity Scale.

The REDCap validated software application will be used to generate a randomized list of variable sized blocks. In order to enroll a patient on the trial, the investigators will have to access the trial site and fill out a simple medical registration form.

#### Intervention

Patients will go through an initial screening at the first visit, followed by administration of two questionnaires: an HH-specific QoL form and the HDSS. Later, they will be randomized into one of three groups.

Both questionnaires, the QoL and the HDSS, will be administered at baseline and again on day 35, which is the last study visit.

### Quality of life questionnaire

To assess quality of life, each patient will answer a specific questionnaire^15^ . The maximum score is 100 points. If a question is not applicable to a patient’s situation or clinical condition, the authors will make proportional adjustments. The negative impact on QoL before treatment was classified into five satisfaction levels, calculated from the total score on the scale (varying from 20 to 100). A score greater than or equal to 84 indicates very bad QoL; scores from 68 to 83 indicate bad QoL; scores from 52 to 67 indicate good QoL; scores from 36 to 51 indicate very good QoL; and scores from 20 to 35 indicate excellent QoL. Improvements in QoL after treatment were also classified into five different levels. If the total score exceeded 84, QoL was considered much worse; from 68 to 83, slightly worse; from 52 to 67, unchanged; from 36 to 51, slightly better; and from 20 to 35, much better.

### Hyperhidrosis disease severity scale

Patients assessed the severity of their sweating using the HDSS. Developed by the International Hyperhidrosis Society®, the HDSS was designed to be a rapid assessment tool that employs just one question with four possible responses. The responses measure the impact that HH has on the patient’s daily life and their tolerance of the symptoms. The HDSS is simple, facilitating response and minimizing the likelihood of errors, thus optimizing the efficiency of medical assessments. This straightforward approach guarantees patients’ ability to rapidly and precisely convey the severity of their condition to healthcare providers. Varella et al.^16^ translated the HDSS into Portuguese, guaranteeing its applicability and utility in Portuguese-speaking populations. The translation maintains the scale’s integrity and efficacy, enabling consistent assessment of patients using different languages. The response options reflect the patient’s tolerance of diaphoresis symptoms and the extent of the negative impact on their daily life. Level 1 indicates unnoticeable sweating that never interferes with daily activities; level 2 is tolerable sweating that sometimes interferes with daily activities; level 3 is barely tolerable sweating that frequently interferes with daily activities; and level 4 is intolerable sweating that always interferes with daily activities. Patients should assign a specific score for each area affected by HH. For data analysis, the authors calculate the improvement delta from the HDSS scores: HDSS before treatment (week 0) minus HDSS after treatment (at the follow-up visit) gives the delta. A delta of 0 indicates no improvement; a delta of 1 or 2 indicates slight improvement; and a delta of 3 is considered a significant improvement.

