### Primary efficacy endpoints

The endpoints for assessment of therapeutic efficacy will be improvement in HH severity up to day 35, measured by the HDSS [Time: day 35]. A treatment responder is defined as any participant whose initial HDSS score was 3 or 4 and who achieves an improvement of at least 1 point by day 35 and QoL will be assessed using improvement metrics from a quality of life questionnaire published in 2003.

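### The HDSS delta grades cannot register a full response from baseline 3 and have no place for worsening, and neither HDSS summary nor QoL is named as the one primary measure

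*Protocol article*

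**What the plan says.** Under Hyperhidrosis disease severity scale, the protocol article describes an instrument that "employs just one question with four possible responses", numbered 1 (best) to 4 (worst). It fixes the change score: "HDSS before treatment (week 0) minus HDSS after treatment (at the follow-up visit) gives the delta". It then grades that change for data analysis: 0 is no improvement, and "a delta of 1 or 2 indicates slight improvement; and a delta of 3 is considered a significant improvement". Patients give a separate score for each affected area.

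Under Primary efficacy endpoints (a plural heading), the article names "improvement in HH severity up to day 35, measured by the HDSS". It defines a responder as "any participant whose initial HDSS score was 3 or 4 and who achieves an improvement of at least 1 point by day 35". The same sentence runs on to say that "QoL will be assessed using improvement metrics from a quality of life questionnaire published in 2003".

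The abstract describes the primary outcome only in general terms, as an evaluation of how effective the spray is. The eligibility text requires the HDSS to be answered but sets no minimum score; the severity threshold for entry is on QoL (at least 52). Study expectations looks for superiority of the spray over placebo and a trend towards non-inferiority to oral treatment.

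**The concern.** There are two linked problems.

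- **The grades are badly built.** The top grade depends on where the patient started as well as on how well the patient did. Someone who moves from 3 to the best level on the scale gets the same grade as someone who moves from 4 to 3 and still has barely tolerable sweating. A patient who gets worse falls outside the grading.
- **The primary measure is not uniquely fixed.** The article gives an HDSS change, a set of grades for it, a responder rule and a QoL score. It does not say which HDSS summary carries the primary conclusion, or how QoL ranks against it.

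The design is described as open with blinded endpoint assessment, both outcomes are patient-reported, and the arms are very small. In that setting, an unfixed headline measure leaves room to choose it after seeing results. Chance differences in baseline HDSS would also feed directly into the proportion reaching the top grade.

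**Working it through.** The article states no alpha, power or effect size for this endpoint, so there is no figure of its own to reproduce. The check is one of logic.

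**Inputs.** HDSS levels 1 to 4; delta = baseline minus follow-up; grades 0 = none, 1 or 2 = slight, 3 = significant (all from the HDSS section). Responder = baseline 3 or 4 and delta of at least 1 (Primary efficacy endpoints). Allocation 1:1:1 (Randomization) among about 20 to 21 patients (abstract and Study design).

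**Step 1: both rules applied to each transition from baseline 3 or 4.**

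| Baseline to day 35 | Delta | Grade in HDSS section | Responder rule |
|---|---|---|---|
| 3 to 1 | 2 | slight | responder |
| 3 to 2 | 1 | slight | responder |
| 3 to 3 | 0 | none | non-responder |
| 3 to 4 | -1 | no grade | non-responder |
| 4 to 1 | 3 | significant | responder |
| 4 to 2 | 2 | slight | responder |
| 4 to 3 | 1 | slight | responder |
| 4 to 4 | 0 | none | non-responder |

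- The largest delta from baseline 3 is 3 - 1 = 2, so the top grade is out of reach for every such patient.
- Five transitions make a responder. Four are graded slight and one (4 to 1) significant.
- The only ungraded case here is 3 to 4.

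**Step 2: baseline 1 or 2.** The listed entry criteria do not exclude these. A change from 2 to 1 is slight improvement under the grades but a non-response under the responder rule.

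**Step 3: effect of baseline mix.** 21/3 = 7 and 20/3 = 6.7, so arms hold 6 or 7 patients. The most an arm can score on the top grade is its proportion at baseline 4. Each patient who enters at 3 instead of 4 lowers that ceiling by 1/7 = 14 or 1/6 = 17 percentage points, whatever the treatment does.

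**Step 4: raw delta against baseline adjustment, if HDSS is analysed as a score.** Let ρ be the baseline to day-35 correlation and k the ratio of baseline to follow-up SD. The variance of the adjusted analysis relative to the raw change is (1 - ρ²)/(1 + k² - 2ρk). Neither ρ nor k is in the article, so the values below are assumptions.

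| ρ | k = 1 | k = 0.5 |
|---|---|---|
| 0.3 | 0.91/1.40 = 0.65 | 0.91/0.95 = 0.96 |
| 0.5 | 0.75/1.00 = 0.75 | 0.75/0.75 = 1.00 |
| 0.7 | 0.51/0.60 = 0.85 | 0.51/0.55 = 0.93 |

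The saving is 15 to 35% if the two SDs are equal, and only 0 to 7% if the baseline SD is half the follow-up SD. In no case shown is adjustment worse than the raw delta.

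**The case against.** The strongest reply is that nothing here is contradictory. The HDSS section labels sizes of improvement and never defines success. Only the primary endpoint section defines a responder. From baseline 3 or 4, every patient with a delta of 3 is also a responder, so the rules are nested: a binary rule beside a grade. The numeric delta still records worsening even though no label does. The model and the handling of multiplicity are commonly left to an analysis plan, which is not shown. This stands as far as it goes. It does not repair a grade that baseline-3 patients cannot reach, and it does not say which summary is primary.

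Four stronger readings are tempting, but the article does not support them:

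- **That the two HDSS rules are incompatible, so the trial could pass on one and fail on the other.** This treats a descriptive label as a criterion for trial success, which the article does not do.
- **That there are three primary measures.** This promotes the grade to an endpoint. At most, the primary section names HDSS and QoL. Because of the run-on sentence, QoL could even be read as part of the responder definition.
- **That the familywise error reaches 26%** (1 - 0.95^6 = 0.265). This needs six independent tests at 5%. The HDSS summaries come from the same scores, both comparisons share the topical arm, no alpha is stated, and the comparison with oral treatment is worded as an expected trend, not a test.
- **That counting cells of the full 4-by-4 transition grid measures how often the fault bites.** Nothing supports giving equal weight to all baselines, and the responder rule sets levels 1 and 2 aside.

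**Conclusion.** The point holds in limited form. The grading rule fixed for data analysis is defective: its top grade is reachable by one transition only, it is closed to all baseline-3 patients, and it omits worsening (the 3 to 4 case among those at baseline 3 or 4). Four of the five responder transitions rank only as slight improvement. The rules can coexist, but the article names neither as the primary HDSS summary and leaves QoL unranked beside them. An unseen analysis plan might settle the ranking; it could not make a delta of 3 reachable from baseline 3.

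The consequences are a top-grade proportion that moves with chance baseline mix in arms of 6 or 7, and a headline measure open to choice after the data are seen. The logical findings need no assumption beyond the stated scale and rules. The size of any gain from baseline adjustment does depend on the assumed correlation and variance ratio. This should be corrected, but it does not by itself make the trial uninterpretable.

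**What to change.** Before outcome data are seen:

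1. Name one primary HDSS measure, on the axillary score at day 35, for topical oxybutynin versus topical placebo. Either the existing responder rate or the day-35 score adjusted for baseline HDSS would serve; the choice is the sponsor's. If the responder rate is chosen, say how patients with baseline HDSS 1 or 2 are counted.
2. State whether QoL is secondary, or co-primary with an explicit decision rule, and separate its sentence from the responder definition.
3. Delete the delta grades, or replace them with the observed baseline-by-day-35 table for each arm, including worsening.
4. Where HDSS is analysed as a score, adjust for baseline HDSS and do not compare raw deltas.

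The cost is a change of wording, with no new data or visits. The downside is that QoL or one of the HDSS summaries may lose its primary label.
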